**Methods/Design:**

This paper presents the protocol of the evaluation study consisting of a quantitative effect evaluation and a qualitative process evaluation. The effect evaluation has a pre-test post-test design, with measurements before implementation (month 0) and after implementation (month 9) of a best practice. Patients are eligible if they have a life expectancy of less than six months and/or if they are undergoing palliative treatment and provided they are physically and mentally capable of responding to questionnaires. Bereaved relatives are eligible if they have been involved in the care of a deceased patient who died after a sickbed between six weeks and six months ago. Three types of measurement instruments are used: (1) numerical rating scales for six symptoms (pain, fatigue, breathlessness, obstipation, sadness and anxiety), (2) the Consumer Quality Index Palliative Care - patient version and (3) the version for bereaved relatives.

The process evaluation consists of analysing implementation plans and reports of the implementation, and individual and group interviews with healthcare professionals. This will be done nine to eleven months after the start of the implementation of a best practice.

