**Figure 1 F1:**
[figure not shown]
Organogram of the national quality improvement program palliative care.

An existent set of quality indicators measured among patients and bereaved relatives will be used for the effect evaluation [20]. The inclusion and exclusion criteria for patients and bereaved relatives are described in Additional files 2 and 3. Per trajectory we aim to include 15–20 patients and 30–40 bereaved relatives in each assessment period. As there are two assessment periods for the approximately 17 planned trajectories per year, this will result into a minimum of about 510 participating patients and 1020 participating bereaved relatives per year, which gives a total number of about 2040 patients and 4080 bereaved relatives over four years.

For the process evaluation, data will be collected among professionals. For each implementation trajectory, the project manager will be interviewed and a group interview will be done with other stakeholders involved. Assuming 17 implementation trajectories per year over four years, this will result in 68 interviews with project managers and 68 group interviews with stakeholders.

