### Effect evaluation

Pre-test and post-test measurements will take place in the effect evaluation, in month 0 and month 9 respectively (see Figure 2). During these two measurement months, eligible patients and bereaved relatives will be asked to participate.

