#### Data analysis

Descriptive statistics (frequencies, percentages and means) will be used to analyse background characteristics.

The effects of the separate implementation trajectories (research question 2) will be analysed using descriptive analyses as well as univariate analyses (with paired t tests or McNemar’s test). To assess the differences between pre-test and post-test measurements for the whole programme (research question 1), multilevel analysis will be used, including the levels of the participating care networks or care organizations, and the type of best practice. SPSS, STATA and ML-WIN will be used for the statistical analysis.

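### Paired t tests and McNemar's test are assigned to the trajectory-level comparison, but relatives cannot be paired and no pairing is defined for patients

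*Protocol article*

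**What the plan says.** The Data analysis section under Effect evaluation gives research question 2 descriptive analyses plus "univariate analyses (with paired t tests or McNemar"'s test). No independent-samples test is named. Research question 1, the primary objective, gets a multilevel model whose named levels are the network or organisation and the type of best practice. No person level is named.

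The sampling is described in three places:

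- **Timing (Effect evaluation).** "Pre-test and post-test measurements will take place in the effect evaluation, in month 0 and month 9 respectively". Recruitment takes place afresh at each: "During these two measurement months, eligible patients and bereaved relatives will be asked to participate".
- **Eligibility (Abstract, Methods/Design).** For patients: "Patients are eligible if they have a life expectancy of less than six months and/or if they are undergoing palliative treatment". A relative must have been involved in the care of "a deceased patient who died after a sickbed between six weeks and six months ago".
- **Numbers (Study population).** Each trajectory aims for 15–20 patients and 30–40 relatives in each assessment period. With two periods and about 17 trajectories a year, "this will result into a minimum of about 510 participating patients and 1020 participating bereaved relatives per year".

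The article describes no follow-up of month-0 respondents, no linking identifier and no matching rule.

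**The concern.** A paired t test works on within-pair differences, and McNemar's test on discordant pairs of a binary outcome. Without pairs, neither statistic is defined. The sampling reads as two separate cross-sections per trajectory, while the analysis sentence assumes one cohort seen twice.

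The stake is the inferential part of research question 2. Relatives are the larger sample and, according to Table 2, the only source for the place-of-death indicators. For them the named tests cannot be run. For patients, an analyst who follows the sentence has two options. One is to keep only those who answered at both times, a selected group of longer survivors. The other is to pair unrelated people by some arbitrary rule and drop the surplus when the two periods differ in size.

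**Working it through.** **1. The plan's own head count.** Inputs are from Study population: lower target per trajectory and period, 2 periods, 17 trajectories, 4 years.

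- Patients: 15 × 2 × 17 = 510 per year; 510 × 4 = 2040.
- Relatives: 30 × 2 × 17 = 1020 per year; 1020 × 4 = 4080.

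All four stated totals are reproduced. One cohort measured twice would be 15 × 17 = 255 patients and 30 × 17 = 510 relatives per year (1020 and 2040 over four years). The plan therefore counts the two periods as separate participants.

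**2. Relatives.** Six weeks is 42 / 30.44 ≈ 1.4 months.

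| Measurement | Eligible deaths |
|---|---|
| Month 0 | month −6 to −1.4 |
| Month 9 | 9 − 6 = 3 to 9 − 1.4 = 7.6 |

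If recruitment runs through a whole measurement month, the upper ends move to −0.4 and 8.6, still with no overlap. Put the other way, a month-0 relative would be 9 + 1.4 = 10.4 to 9 + 6 = 15 months past that death at month 9, beyond the six-month limit. The number of possible pairs about the same death is zero.

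**3. Patients.** The documents give no survival distribution and no split between the two eligibility routes. As an illustration only, assume exponential survival, so the share alive at month 9 is 0.5^(9/median):

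| Assumed median (months) | Alive at month 9 | Of 15–20 patients |
|---|---|---|
| 3 | 12.5% | 2–3 |
| 6 | 35% | 5–7 |
| 9 | 50% | 8–10 |
| 12 | 59% | 9–12 |

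These are ceilings on pairs, before loss of capability, non-response or lack of linkage. The first two rows suit patients admitted on life expectancy. The last two show what the palliative-treatment route, which has no stated prognosis limit, might allow.

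**4. What independent samples can detect.** The article states no alpha, power or effect size. Assume two-sided alpha 0.05, 80% power and a normal approximation. The detectable difference in SD units is (1.96 + 0.84) × √(2/n). For comparison, truly paired data with an assumed correlation of 0.5 multiply this by √(1 − 0.5).

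| n per period | Independent | Paired, correlation 0.5 |
|---|---|---|
| 15 | 1.02 | 0.72 |
| 20 | 0.89 | 0.63 |
| 30 | 0.72 | 0.51 |
| 40 | 0.63 | 0.44 |

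**5. What arbitrary pairing would do.** In 40,000 simulated comparisons of two independent, equal-sized normal samples, randomly paired t tests kept their size at 4.8–5.1%. Power for an assumed 0.5 SD shift fell slightly: 25.1% against 26.5% for the independent test at n = 15, and 58.8% against 59.8% at n = 40. Pairing on sorted values raised the size to 55–70%.

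**The case against.** Several things can fairly be said for the plan.

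- **The question is secondary and also analysed descriptively.** This stands. Percentages and means per period do not need the paired tests. Feedback and dissemination provides for reports after the pre-test too, and those cannot contain a pre-post test. A reader might infer that every trajectory result and feedback report rests on the wrong test, but the documents do not support that.
- **Some patients may take part twice.** This stands in part. The palliative-treatment route has no stated prognosis limit, and the full criteria are in an additional file that is not shown. A reader might infer that the two patient samples are wholly different people, or that repeat participants must be a minority. The head count supports largely separate samples but does not prove that nobody appears twice, and the size of any overlap cannot be derived.
- **Arbitrary pairing need not raise false positives.** This stands for random pairing, as the simulation shows. The article proposes no such procedure, and the result would depend on a rule nobody has specified.
- **The pairing unit could be the organisation.** This fails. It is stated nowhere, and it would leave few pairs, since trajectories with more than five organisations are subsampled. It also does not suit McNemar's test, which compares paired individual yes/no outcomes.
- **An article condenses the full protocol.** Detail may sit elsewhere, but two specific tests are named here and they conflict with the sampling described here.

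**Conclusion.** The named tests do not fit the design. For relatives this follows from the eligibility window and the nine-month interval alone: no pair about the same death is possible. For patients the fault is that no pairing is defined or planned. How many could in principle be measured twice is unknown and depends on the eligibility mix.

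Invalid here means that valid pairs do not exist, not that the type I error rate must rise. The fault is confined to the inferential part of research question 2 and does not reach the primary whole-programme multilevel analysis. The detectable differences rest on the assumed alpha, power and normal approximation, and the paired comparison also on the assumed correlation.

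**What to change.** Replace the paired tests with independent-samples methods: a Welch t test for means, and a chi-square or Fisher's exact test for proportions. Alternatively, use a regression with a period term (post versus pre). Adjustment for the collected background characteristics is desirable, because two separate samples can differ in case mix. Adjust for organisation where the number of organisations in the trajectory allows. State in the design section that the evaluation is repeated cross-sectional.

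If any patients take part twice and can be linked, account for that dependence. This would need an identifier that the article does not describe, and the Ethical considerations section has identifiers removed or disguised in the analysis process, so it should be conditional.

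The core change is the wording of the analysis sentence plus the design statement. It needs no extra participants and no new data. The cost is precision: a single trajectory can reliably show only large changes (about 0.9–1.0 SD with 15–20 patients per period, 0.6–0.7 SD with 30–40 relatives, under the assumptions above). Trajectory-level reports should therefore give estimates with confidence intervals and not treat a non-significant result as evidence of no effect.

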### Process evaluation

A qualitative process evaluation will be conducted nine to eleven months after the start of the implementation in a separate implementation trajectory (see Figure 2). The process evaluation will be used to explain the effects found (or not found) in the effect evaluation and provide insight into how the best practices are implemented.

#### Data collection

First, an analysis of relevant documents (e.g. implementation plans, and interim and final reports of the separate implementation trajectories) will provide insight into the implementation process. Second, we will conduct individual semi-structured interviews with the project managers of each trajectory. The topic list for the interviews will include questions on whether the best practice was implemented as planned, what the barriers and facilitators were for the implementation, what implementation strategies were used and whether the project managers felt implementation has been successful and effective. Third, for each implementation trajectory we will organize semi-structured group interviews with relevant other stakeholders (such as representatives of clients’ participation councils, nurses, doctors or other care professionals involved). A similar topic list as described for the individual interviews will be used for the group interviews. Both individual and group interviews will be audio-recorded.

#### Data analysis

The audio-recorded interviews will be transcribed verbatim. Subsequently a qualitative thematic analysis will be done, starting immediately after conducting and transcribing the individual and group interviews for a specific implementation trajectory. All relevant documents and interviews will be coded, analysed and discussed by at least two researchers. The coding process will be inductive, in the sense that themes and associated codes will emerge from the interview data through repeated comparison of relevant fragments within and between interviews. The coding process will be supported by the software package MAXQDA [23].

### Feedback and dissemination

The project manager and other stakeholders in a specific implementation trajectory will receive internal feedback reports on the results of the effect evaluation (after the pre-test measurements as well as after the post-test measurements) within two months after the measurement period. The prospect of getting feedback reports is important in order to increase the commitment of the project managers and stakeholders to participating in the measurements. In addition, the feedback reports will motivate the professionals involved to further improve the quality of their care, where needed.

Furthermore, interim reports about the progress of the programme as a whole will be published; these will also be made available to the general public. Also, additional international scientific publications about the effects and implementation of the programme are planned.

### Ethical considerations

The study protocol has been approved by the Medical Ethical Committee of the University Medical Center in Leiden, the Netherlands. Written informed consent of all patients will be obtained for the assessment of their symptoms and inpatients also consented with the Consumer Quality Index Palliative Care questionnaire, as it has to be completed by a trained interviewer. Patients who are at home and bereaved relatives received this questionnaire by post and for this no written informed consent is needed. Furthermore, in data collection and analyses procedures we follow the rules of Dutch Personal Data Protection Act (Wet Bescherming Persoonsgegevens). All personal identifiers will be removed or disguised in the analysis process to safeguard the privacy and anonymity of participants.

## Discussion

This evaluation study provides a unique chance to gain insight into the effects and implementation process of the National Quality Improvement Programme for Palliative Care and its separate implementation trajectories. The implementation of best practices within the framework of a long-term, broad nationwide programme can be considered as a complex intervention within a continuously changing, uncontrolled environment. Complex interventions are described by Pawson et al. as long journeys, embedded in multiple social systems, which are open and adaptive [24]. These characteristics also hold for the National Quality Improvement Programme for Palliative Care, which consists of the implementation of multiple best practices in different settings and with different starting points over a four-year period. Our programme is also relatively open and adaptive, for example as a result of the feedback reports and interim reporting. Feedback reports give the organizations insight into the current state of the quality of palliative care within their organization and might lead to additional actions to improve palliative care.

Randomised controlled designs (RCT) are often not applicable and feasible for the evaluation of complex interventions such as national quality improvement programmes [25,26]. When an RCT is not possible - as is the case in the evaluation of the National Quality Improvement Programme for Palliative Care - it is important to use a mixed-method design and to combine quantitative effect measurements with a qualitative process evaluation. Qualitative process evaluations, e.g. based on the qualitative analysis of interviews and documents, can help understand the effects (or sometimes the lack of effects) of interventions. Process evaluations are helpful in elucidating the implementation process and the interventions actually delivered (opening the ‘black box’) and in identifying other possible factors that may have contributed to the measured outcomes. One such factor may be an ‘investigation effect’ caused by the feedback reports. Therefore, during the process evaluation we will pay extra attention to possible additional actions of care organizations prompted by these feedback reports.

Evaluating complex interventions among patients with a limited life expectancy and among bereaved relatives is particularly challenging for researchers. In such populations, researchers have to take extra account of the burden of measurement for respondents, although many of them are willing to contribute to scientific research [27,28]. An additional challenge in our study in particular is the fact that palliative care patients are often 'scattered' throughout the organization or various teams or units. Due to the aim of the National Quality Improvement Programme for Palliative Care, i.e. to improve palliative care in general health care settings (like hospitals or home care), groups of patients with palliative care needs are less concentrated than in research within hospices, for instance, or specialist palliative care units. This means that an extra effort has to be made for the recruitment of patients and relatives as well as for informing all the professionals involved.

## Abbreviations

CQ Index: Consumer quality index; SPSS: Statistical package for the social sciences; ML-WIN: A software package for fitting multilevel models; MAXQDA: A software package for supporting qualitative data analysis.
